#### Exclusion criteria

Patients with any of the following exclusion criteria will be excluded from the study: hallux amputation or total amputation of the foot; a history of surgical procedures in the knee, ankle, or hip; a history of arthroplasty and/or indication of lower limb arthroplasty throughout the intervention period; a diagnosis of neurological and/or rheumatologic diseases; wearing an off-loading device; major vascular complications; severe retinopathy; ulceration not healed for at least 6 months and/or active lower limb ulcers. Additionally, patients who use lower limb orthosis during the intervention period, are unable to provide consistent information, undergo a physiotherapy intervention throughout the intervention period, or report a score between 12 and 21 (probable depression) on the Hospital Anxiety and Depression Scale will also be excluded from the study.

### Procedure

The trial protocol will follow all recommendations established by the Standard Protocol Items Recommended for Clinical Trials (SPIRIT) 2013 statement [42] (the checklist can be found in Additional file 1). Figure 1 presents the design and flowchart of the protocol according to the CONSORT 2010 standards [43].

**Fig. 1 Fig1:**
[figure not shown]
Consolidated Standards of Reporting Trials (CONSORT) flow diagram flow chart illustrating the process of the Footcare (FOCA) trial I. DM diabetes mellitus, DPN diabetic peripheral neuropathy

### Randomization, allocation, and blinding

pt?>The randomization schedule has been prepared using Clinstat software [44] by an independent researcher (Researcher 1) who is not aware of the numeric coding for the control group and intervention group. A numeric block randomization sequence is kept in opaque envelopes.

Potential participants will be assessed through an initial screening that consists of checking the eligibility criteria, classifying the DPN severity, and identifying those with a lower probability of adherence to the intervention due to depression. After the initial screening, participants who meet the inclusion criteria will be randomized to either the intervention group or control group. After the agreement to participate and assignment in the research, the allocation of the groups will be made by another independent researcher (Researcher 2) who is also unaware of the codes. All participant personal data will be kept confidential before, during, and after the study by encoding the participants’ names. Only the physiotherapist (Researcher 3), who is the main researcher responsible for the intervention, is aware of who is receiving the intervention. Researcher 3 is also responsible for the remote monitoring of the intervention by the SOPeD software and by telephone. One physiotherapist and an occupational therapist (Researchers 4 and 5), who are also blind to the treatment allocation, will be responsible for all clinical, functional and biomechanical assessments. Researchers 3, 4, and 5 are blind to the block size used in the randomization procedure. The trial statistician will also be blind to treatment allocation until the main treatment analysis has been completed. The trial design is open label where only the outcome assessors are blinded so unblinding will not occur.

### Trials arms

#### Control group

Participants in the control group will not receive any specific intervention besides the treatment recommended by the health care team (doctors, nurses, and podiatrists), which will include pharmacological treatment as well as self-care and foot care recommendations as per international consensus. If proven effective, the benefits of the foot-related exercises protocol will be explained and offered to all control group participants at the end of the study.

#### Intervention group

Patients in the intervention group will perform customized foot-related exercises included in the SOPeD software three times per week at home for a 12-week period. These will be remotely supervised by Researcher 3 after the first in-person supervised session at the department. They will receive access and all instructions on how to use the tool on the first day. During the follow-up period, intervention group participants will be encouraged to follow the same schedule set by the project till the end of the study (24 weeks after allocation), but will not be remotely monitored, and will be encouraged to continue exercising in the future.

### Outcomes and measures

#### Participant timeline

Participants in the intervention group and control group will be assessed at the preintervention baseline (T0), at the end of the 12-week intervention (T12), and at follow-up 24 weeks after baseline (T24). A physiotherapist and an occupational therapist (Researchers 4 and 5) who are blinded to group allocation will perform all the assessments. All participants will maintain contact with Researcher 3 throughout the follow-up period through the web software, email, and telephone. Table 1 shows the schedule of enrollment, interventions, and assessment according to the SPIRIT guidelines [42].

**Table 1 Tab1:**
[figure not shown]
Schedule of enrollment, interventions and assessment of the Footcare (FOCA) trial I, following the Standard Protocol Items Recommended for Clinical Trials (SPIRIT) guidelines

#### Screening measures

An initial anamnesis will be performed to check the eligibility criteria, including clinical, anthropometric, and demographic characteristics of all participants. The classification of DPN severity will be determined using the Decision Support System for Classification of Diabetic Polyneuropathy [45, 46] (www.usp.br/labimph/fuzzy). Participants with scores ≥2.0 (mild DPN) will be included in the study. Those who score between 12 and 21 (probable depression) on the Portuguese version of the Hospital Anxiety and Depression Scale will not be included [47].

### Measures of primary and secondary outcomes

The quantification of DPN symptoms and classification of DPN severity will be the primary outcomes. Foot–ankle kinematics and kinetics during gait, plantar pressure distribution during gait, tactile and vibration sensitivities, foot health and functionality, foot strength, and functional balance constitute the secondary outcomes.

#### DPN symptoms

DPN symptoms will be assessed by the Brazilian version of the Michigan Neuropathy Screening Instrument [48]. This self-administered questionnaire is comprised of 15 questions about symptoms and events related to foot sensitivity. The answers are summed to get a total score ranging from 0 to 13 (with 13 representing the worst DPN).

#### Fuzzy classification of DPN severity

The decision support system for the classification of DPN is based on fuzzy logic using three domains: signs and symptoms extracted from the Michigan Neuropathy Screening Instrument, tactile sensitivity through the number of nonsensitive areas using a 10-g monofilament, and vibration sensitivity evaluated by a tuning fork (128 Hz) and classified as absent, present or diminished. The software produces a score from 0 to 10, with a higher score indicating more severe DPN.

#### Tactile sensitivity

Tactile sensorial deficits will be evaluated by a 10-g monofilament [49] in four plantar areas (plantar face of the hallux and first, third, and fifth metatarsal heads). The areas will be evaluated in a random order, and the participant will not be allowed to view the monofilament. The number of areas where the participant does not feel pressure will be evaluated [49]. The greater the number of areas marked, the greater the impairment of tactile sensitivity.

#### Vibration sensitivity

Vibration sensitivity will be assessed by a tuning fork (128 Hz) perpendicular to the dorsal region of the distal hallux phalanx at constant pressure. The participant will report the moment they no longer feel the vibration of the tuning fork, and the evaluator must time the interval between which the participant reports that they cease to feel the vibration and the moment the evaluator ceases to feel the vibration in their hand [50]. Values smaller than 10 s will be classified as normal vibratory sensitivity; values greater than 10 s will be classified as decreased vibratory sensitivity; if the participant does not perceive the vibration imposed by the tuning fork, it will be classified as absent vibratory sensitivity [50].

#### Foot health and functionality

The Brazilian version of the Foot-Health Status Questionnaire (FHSQ-BR) [51] will be used to determine foot health. This instrument is divided into three domains, and this study will use domains I and II. Domain I evaluates the foot in four dimensions: pain, function, footwear, and general health. Domain II evaluates the general state of health in four dimensions: general health, physical activity, social capacity, and vitality. Domains I and II are comprised of questions with answers in affirmative sentences and a Likert-type scale. Domain III is comprised of the collection of participants’ general demographic data. Domains I and II receives a score from 0 to 100, where 100 expresses the best condition and 0 the worst. The data will be analyzed using the FHSQ version 1.03 software (Care Quest—Researching Healthcare Solutions, Australia).

In addition to the face-to-face assessment, every 30 days the participants will self-assess their DPN symptoms as well as the health status of their feet by completing both the FHSQ-BR questionnaire and undergoing a physical examination of the foot using the SOPeD software (www.soped.com.br), in which the participant can drag markers that represent major foot changes (calluses, cracks, fissures, mycoses, toe deformities, ulcers, and amputations) onto images of both feet (Fig. 2). At the end of these monthly evaluations, the participant and the main researcher will be provided with a report related to the patient’s conditions and whether or not they are still able to perform the exercise protocol.

**Fig. 2 Fig2:**
[figure not shown]
Layout of the Diabetic Foot Guidance System (SOPeD). (**a**) Self-assessment of common foot problems with diabetes mellitus and diabetic peripheral neuropathy. (**b**) Report of the assessment. (**c**) The foot physical examination

#### Foot isometric strength

The muscle isometric strength of the flexor muscles of the hallux and lesser toes will be evaluated using the emed-q100 pressure platform (novel, Munich, Germany) according to a test protocol previously described by Mickle et al. [52]. The participant will stand with the evaluated foot centered on the pressure platform and will be instructed to push down as hard as possible using only the hallux and toes, particularly on the metatarsophalangeal joints and not the hallux interphalangeal joint. A physiotherapist will determine whether the participant lifted the heel and will inspect fluctuations in the line of gravity and trunk posture during each trial. If any changes are observed in the line of gravity or positioning of the heel or trunk, the trial will be excluded. Three valid trials will be completed on each foot (left and right), and the plantar regions corresponding to the hallux and toes will be identified. To determine such areas, novel-win Multimask software v. 9.35 (novel, Munich, Germany) will be used. Maximum force (N) will be normalized by body weight and analyzed for the hallux and toe areas separately as well as for the whole foot.

#### Functional balance

Functional balance will be evaluated using the Functional Reach Test proposed by Duncan et al. [53]. The patient will stand barefoot with the foot dorsal region perpendicular to the wall, with both feet parallel in a comfortable position, without touching the wall, and with the shoulder flexed at 90° and the elbow extended. The hands will be closed. A tape measure will be attached to the wall parallel to the floor and positioned at the height of the patient’s acromion. The initial measurement will correspond to the position in which the third metacarpal touches the tape. The participant will then be instructed to lean forward as much as possible without losing balance, flexing the hips, or taking a step. Displacement will be checked on the tape measure. Three trials will be performed, and the mean of the trials will be used for statistical purposes. The greater the distance achieved, the better the functional balance.

#### Foot–ankle kinematics and kinetics during gait

The foot–ankle kinematic parameters during gait will be acquired by eight infrared cameras at 100 Hz (Vicon® VERO, Vicon Motion System Ltd., Oxford Metrics, Oxford, UK). Ground reaction forces will be acquired by a force plate (AMTI OR-6-1000, Watertown, MA, USA) with a sampling frequency of 100 Hz embedded in the center of a 10-m walkway. Force and kinematic data acquisition will be synchronized and sampled by a 16-bit analog-to-digital converter.

The laboratory coordinate system will be established at one corner of the force plate, and all initial calculations will be based on this coordinate system. Each lower-limb segment (shank and thigh) will be modeled based on surface markers as a rigid body with a local coordinate system that coincides with the anatomical axes. Translations and rotations of each segment will be reported relative to the neutral positions defined during the initial static standing trial. All joints will be considered spherical (i.e., with three rotational degrees of freedom). Forty-two reflexive-passive markers (diameter = 9.5 mm) will be positioned on both lower limbs following the Plug-In Gait setup protocol and the Oxford Foot Model (OFM) setup protocol [54]. The foot will be modeled by the OFM, which has been tested for reproducibility regarding its applicability to foot biomechanics analysis during gait [55, 56].

After the volume calibration and the static trial acquisition, participants will be advised to walk at their comfortable self-selected speed along a 10-m track, with a maximum variation of 5% between measurements, thus ensuring that the same speed is maintained in all assessments (T0, T12, T24) of the same participant. Two photoelectric cells (CEFISE, Model Speed Test Fit, Nova Odessa, Brazil) 6 m apart will be used to verify the self-selected speed and to check the trials and assessments. After complete habituation to the laboratory environment, five valid steps will be acquired on each side during gait.

The automatic digitizing process, three-dimensional reconstruction of the markers’ positions, and filtering of kinematic data will be performed using motion capture Nexus software (NEXUS 2.6, Vicon Motion System Ltd., Oxford Metrics). Kinematic data will be processed using a zero-lag second-order low-pass filter with cutoff frequency of 6 Hz. Ground reaction force data during walking will be processed using a zero-lag low-pass Butterworth fourth-order filter with cutoff frequency of 50 Hz.

The bottom-up inverse dynamics method will be used to calculate the net moments in the sagittal of the ankle considering the inertial properties of the segments [57]. For the calculation of the ankle power, the calculated joint moment and the angular velocity of the ankle in the sagittal plane will be considered. The temporal series of the joint angles and moments will be calculated using the Plug-In Gait and OFM in the Vicon Nexus software. Calculation of all discrete variables from the time series will be performed using a custom written MATLAB function (MathWorks, Natick, MA, USA).

The following ankle kinematic variables will be analyzed: 1) maximum dorsiflexion during the heel-strike phase; 2) maximum plantarflexion during the push-off phase; 3) maximum dorsiflexion during the toe-off phase; and 4) dorsiflexion range of motion in the sagittal plane during the stance phase. The foot kinematic variables that will be analyzed include: 1) hindfoot to forefoot rotation; 2) transverse plane angle between the first and second metatarsal bones; 3) transverse plane angle between the second and fifth metatarsal bones; 4) maximum inversion of the calcaneus (frontal plane); 5) maximum eversion of the calcaneus (frontal plane); and 6) deformation of the medial longitudinal arch. The ankle kinetic variables that will be analyzed are the ankle flexor moment peak normalized by body weight times height during the heel-strike phase and the ankle extensor moment peak at approximately 80% of the gait support phase, corresponding to the propulsion phase.

#### Plantar pressure distribution during gait

A pressure platform (emed-q100, novel) will be used to evaluate the pressure distribution during walking. The pressure platform is 700 × 403 × 15.5 mm with 6080 sensors and a resolution of four sensors per square centimeter when data is collected at 100 Hz. Participants will be invited to walk barefoot across the platform at a comfortable self-selected speed (the same as in the kinematic trials), and data for both feet will be collected. For the analysis of the regions of interest, an anatomical mask that divides the foot into seven anatomical plantar regions—heel, midfoot, medial forefoot, medium forefoot, lateral forefoot, hallux, and two to five toes—will be analyzed. The anatomical mask will be performed from the integration of the plantar pressure and kinematic gait of the multisegmented OFM. Peak pressure (kPa) and pressure–time integral (kPa*s) will be analyzed for each region of interest in both feet [58].

#### Intervention

Participants allocated to the intervention group will receive a customized foot–ankle therapeutic exercise protocol for strengthening and improving functionality based on the SOPeD software.

The exercise protocol (eight exercises per session) will be performed three times a week for 12 weeks and remotely supervised by the physiotherapist (Researcher 3). Each session will last for 20 to 30 min. The participants in the intervention group will be encouraged to continue exercising using the same regimen established in the 12-week intervention during the follow-up period (12 additional weeks).

The therapeutic exercise protocol and SOPeD have been described in detail elsewhere [40]. The software personalizes the progression of the exercises according to the individual’s physical capacity. It establishes the volume of training, the criteria for progression, and the guidelines for interrupting the protocol, thus resembling a face-to-face intervention. A total of 104 exercise variations comprised of 1) muscle stretching, 2) strengthening of the intrinsic muscles of the foot, 3) strengthening of the extrinsic muscles of the foot and ankle, and 4) functional exercises (e.g., balance and gait training) are available through the software (Fig. 3).

**Fig. 3 Fig3:**
[figure not shown]
Diabetic Foot Guidance System (SOPeD). (**a**) perceived effort scale to be filled after each exercise completion. (**b**) Layout of the exercises page with a video, audio and written instructions for each exercise

The progression of the exercises is based on individual capabilities, which are graded by a visual analogue effort scale after each exercise is performed (Fig. 3). The discontinuation criteria for the exercises include cramps, moderate to intense pain, fatigue, or any other condition that exposes the patients to any discomfort.

**Fig. 4 Fig4:**
[figure not shown]
Diabetic Foot Guidance System (SOPeD) interface. (**a**) Game rules. (**b**) Exercise page in game format

To improve adherence, the SOPeD was developed using gamification components (Fig. 4) to encourage patients to keep using the tool [59].

Users also have the opportunity to send messages to the main researcher or any member of the specialized team about their training, DPN, or any technical difficulties while using the software. The user can also participate in a forum to exchange experiences with other people who are in the same group as them (Fig. 5).

**Fig. 5 Fig5:**
[figure not shown]
Diabetic Foot Guidance System (SOPeD) interface. (**a**) Section for communication with specialists. (**b**) Communication forum

One discontinuation criterion for the intervention is the occurrence of a foot ulcer as assessed by a blinded podiatrist nurse who specializes in diabetic feet. The participants will be advised to report to Researcher 3 with any sign of tissue damage.

If an intervention group participant fails to log in to the web-based software for more than 3 consecutive days, an email will be automatically sent asking the participant to log in to their account. The physiotherapist responsible for the therapeutic protocol will also make telephone contact with participants who do not respond to email reminders from the web-based software. If an intervention group participant fails to access the software for 2 consecutive weeks without explanation, that participant will be terminated from the study.

After the 12-week intervention period and follow-up, all participants will be questioned about their satisfaction with the protocol: “Did you enjoy doing the exercises?” There will be three possible answers: no, a little, and a lot. To avoid evaluation bias, participants will answer this question secretly through an anonymous online form sent to their email. Patients will be informed about their anonymity, and this form will only be accessed after the completion of the study.

For the duration of the trial, participants from the intervention group and control group will be advised not to engage in any new physical therapy program for the foot and ankle. If any participant cannot avoid such behavior, they must report this situation to the main researcher and will be excluded from the study.

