### Sample size and statistical analyses

The sample calculation was performed using the GPower v.3.1 program [60]. Two outcomes of extreme functional importance for patients with DPN were used to calculate the sample size. Considering the primary outcome (DPN symptoms), a medium effect size (0.52) was adopted and, for the secondary outcome (peak pressure at forefoot), a small effect size (0.20) was adopted. Both effect sizes were taken from the study by Sartor et al. [30] which evaluated the effect of a 12-week supervised physical therapy exercise in patients with DPN. In order to obtain the largest sample size, the smallest effect size (0.20) was used. A statistical design of F-test repeated measures and interaction between and within factors with two repeated measures and two study groups, a statistical power of 0.80, an alpha of 0.05, and an effect size of 0.20 were used for the sample size calculation. The resulting sample size was 52 individuals. A final sample size of 62 patients was then chosen after estimating a drop-out rate of 20%.

The inferential statistical analysis will be based on an intention-to-treat analysis and per-protocol analysis. Mixed general linear models of analysis of variance for repeated measure will be used to detect treatment–time interactions (α = 5%), and the Newman–Keuls post hoc test will be used to obtain group effect (intervention group and control group), time effect (between T0 and T12), and group–time interaction. Effect sizes (Cohen’s *d* coefficient) will also be provided between T0 and T12 and between T12 and T24 to determine if the intervention shows any treatment effect. The difference between the means with their respective 95% confidence intervals will also be calculated. Imputation of any missing data for the analyzed variables will be conducted depending on the nature of the losses: missing completely at random, missing at random, or missing not at random. The per-protocol analysis will include only those patients who completed follow-up in the allocated intervention group. If there is evidence that the difference in the treatment depends on certain patient characteristics identified in the baseline assessment, a subgroup analysis will be performed.

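### Removing participants from the study for not logging in (intervention arm only) or for starting foot physiotherapy conflicts with the planned intention-to-treat analysis

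*Protocol article*

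**What the plan says.** The Intervention section (text after Fig. 5) sets two rules that end study participation after randomisation.

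- **Log-in rule, intervention arm only:** "If an intervention group participant fails to access the software for 2 consecutive weeks without explanation, that participant will be terminated from the study". It is preceded by an automatic e-mail after more than 3 days without log-in and by a telephone call to those who do not answer.
- **Physiotherapy rule, both arms:** "participants from the intervention group and control group will be advised not to engage in any new physical therapy program for the foot and ankle"; those who cannot comply are told that "they must report this situation to the main researcher and will be excluded from the study".

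The Exclusion criteria section also lists events that cannot be known at entry: "patients who use lower limb orthosis during the intervention period" and those who "undergo a physiotherapy intervention throughout the intervention period".

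Against this, the Trial design and Participant timeline sections plan assessment of both groups at baseline, 12 weeks (T12) and 24 weeks (T24). Sample size and statistical analyses states: "The inferential statistical analysis will be based on an intention-to-treat analysis and per-protocol analysis". It adds: "The per-protocol analysis will include only those patients who completed follow-up in the allocated intervention group". On missing data it says: "Imputation of any missing data for the analyzed variables will be conducted depending on the nature of the losses", naming the three usual missingness classes.

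**The concern.** An intention-to-treat comparison needs outcomes from everyone randomised, whatever they did afterwards. Both rules end participation because of what a participant did, and the article nowhere says that T12 and T24 outcomes are still sought from those removed. The log-in rule can act in only one arm, so the intervention group with observed outcomes becomes a group of persistent users, while the control group is not filtered in the same way.

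Adherence is part of what this trial tests. SOPeD is presented as a tool for autonomous self-management, with public-health use intended if it proves effective. The relevant effect is that of offering the software, including to people who stop using it. An estimate among those who kept logging in answers a narrower question.

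**Working it through.** **1. The passages side by side.**

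- In the Intervention section a foot ulcer is a reason to stop the *intervention*, whereas two weeks of unexplained non-access ends participation in the *study*. The article separates the two ideas and applies the stronger one to non-adherence, so this is hard to read as loose wording.
- A participant who has left the study has no later T12 or T24 assessment. That person cannot contribute the missing outcomes to an intention-to-treat analysis, except through imputation.
- The imputation sentence does not mention terminated or excluded participants. Losses triggered by non-use of the software are plausibly not missing at random.
- The log-in rule is one-sided by design. The physiotherapy rule covers both arms.

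**2. The plan's own figure, to fix the scale.** Inputs from Sample size and statistical analyses: effect size f = 0.20, two groups, m = 2 repeated measures, alpha 0.05, power 0.80, N = 52. The correlation between measures is not stated; 0.5 is assumed.

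- Noncentrality = f² × N × m / (1 − correlation) = 0.04 × 52 × 2 / 0.5 = 8.32.
- Power is 0.8075 at N = 52 and 0.7915 at N = 50, so 52 is reproduced.
- For a two-by-two interaction, the between-group difference in change is 4f = 4 × 0.20 = 0.80 SD. Check: a two-sample test with 26 per arm has squared noncentrality 13 × d²; setting 13 × d² = 8.32 gives d² = 0.64 and d = 0.80.

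**3. Illustration of one-arm removal.** The document gives none of these inputs; all are assumptions. Let a share q of the intervention arm be removed and not recovered by imputation, and let them be g SD worse than those retained. The full-arm mean is then worse than the retained mean by q × g, so the bias in favour of the intervention is q × g.

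| q | g (SD) | Bias (SD) | Share of 0.80 SD |
|---|---|---|---|
| 0.10 | 0.3 | 0.03 | about 4% |
| 0.20 | 0.5 | 0.10 | 12.5% |
| 0.30 | 0.8 | 0.24 | 30% |

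The value q = 0.20 equals the plan's drop-out rate, but the plan does not say how many drop-outs the log-in rule would cause.

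**4. Effect on the false-positive rate,** under the same assumptions with no true effect, 31 per arm, and a simple comparison of means. At q = 0.20 the intervention arm keeps 31 × 0.8 = 24.8. The standard error is √(1/24.8 + 1/31) = 0.269 SD. With g = 0.5 the shift is 0.10 / 0.269 = 0.37 standard errors, and the two-sided type I error is 0.066 instead of 0.05. For g from 0.25 to 1.0 it runs from 0.054 to 0.115.

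**The case against.** The strongest reply has four parts.

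- **Imputation is planned,** and it expressly allows for data not missing at random. An intention-to-treat analysis with imputation could formally retain everyone randomised. This stands as a possibility, but the article does not say that removed participants are covered, and imputing outcomes that the protocol itself chose not to collect is weaker than collecting them.
- **The rule is milder than it may sound.** It applies only without explanation, and after e-mail and telephone contact. That limits how many are removed, not the conflict for those who are. Two weeks is 6 of 36 sessions, so someone with 30 of 36 done (83%) could be removed, but only if the gap falls exactly in weeks 11 and 12. That is an edge case.
- **An article condenses,** and exact analysis sets may be defined elsewhere. This is fair for the definitions. The termination rule, however, is stated here, and no analysis plan can use outcomes that were not collected.
- **Direction and size are not established.** This stands.

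A reader might infer more than the document supports:

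- *That the two rules together favour SOPeD.* If the physiotherapy rule removed worsening controls more often, it would act against the intervention. The document gives no basis for saying which arm it affects more.
- *That 0.10 SD is half the effect the trial is designed to detect.* The stated 0.20 reproduces N = 52 as an F-test effect size, which is about 0.80 SD, so 0.10 SD is about one eighth. The 0.20 was also taken for forefoot peak pressure, a secondary outcome; 0.52 is given for symptoms.
- *That the intention-to-treat and per-protocol sets become the same people.* Those with observed outcomes would overlap heavily, but imputation could keep the sets apart.
- *That orthosis users are removed after randomisation.* That item appears only among the eligibility criteria; explicit removal is written for non-access and for physiotherapy.

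**Conclusion.** The concern holds in this form: the termination and exclusion rules conflict with the intention-to-treat analysis and with the T12 and T24 assessment of all participants. Followed as written, the plan loses outcomes according to post-randomisation behaviour, and under the log-in rule in one arm only. The unspecified imputation does not reliably repair this.

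The log-in rule alone plausibly favours SOPeD, if those who stop logging in would have fared worse than those who continue. The net direction across both rules is uncertain. The q × g figures above show scale only: they are modest against 0.80 SD at the lower end and not negligible at the upper end. The contradiction itself depends on none of these numbers.

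**What to change.** Reconcile the Exclusion criteria, Intervention, and Sample size and statistical analyses sections by separating the end of the intervention from the end of outcome follow-up.

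- Record two weeks of non-access, and any new foot-ankle physiotherapy, as protocol deviations rather than as reasons to leave the study.
- Still invite these participants to T12 and T24.
- State that all randomised participants are analysed in their allocated group, and that any imputation covers these participants where outcomes remain missing.
- Use the SOPeD log-in record and new physiotherapy only to define the per-protocol set, with controls kept in; the present wording can be read as leaving them out.
- Say whether the during-intervention orthosis and physiotherapy items are entry criteria or deviations.

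The cost is a short amendment and some extra contact effort, since both visits are already scheduled. The effect estimate will be somewhat diluted, and some non-adherers may still not attend, so the bias is reduced rather than removed. No clinical stopping rule is changed.
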